CWs (n=100; 50 men, 50 women) meeting the inclusion/exclusion criteria will complete a set of socioeconomic, demographic, and the following clinical questionnaires (primary diagnosis dependent) at baseline: Depression and Anxiety Stress Scale - 42 Item (DASS-42), Quality of Life Satisfaction and Enjoyment Questionnaire (Q-LES-Q), Quick Inventory of Depressive Symptoms Self Report - 16 Item (QIDS-SR16), Patient Health Questionnaire - 9 Item (PHQ-9), Generalized Anxiety Disorder - 7 Item (GAD-7), and PTSD Checklist for the DSM-5 (PCL-5) [55-60]. Questionnaires and e-CBT modules will be completed through the Online Psychotherapy Tool (OPTT; OPTT Inc.), a secure, cloud-based, mental health care delivery, online platform. OPTT can be accessed from various devices (ie, computer, cellphone, tablet) and internet browsers. Following the initial assessment, participants will be randomly allocated to the e-CBT + TAU (n=50; 25 men, 25 women) or TAU (n=50; 25 men, 25 women) arm.

Participants in the e-CBT group will be assigned to 1 of the 6 therapy modules based on their gender and diagnosis (ie, female/male; GAD/MDD/PTSD). All e-CBT sessions will be completed through OPTT. Sessions will be designed to mirror in-person CBT content and consist of approximately 30 slides and interactive therapist videos (40-60–minute completion time), with 12 sessions in total (1 module per week). The modules will focus on standard aspects of CBT (the connection between thoughts, behaviors, emotions, physical reactions, and environment) and incorporate different skills into each session (eg, mindfulness, goal setting, activity scheduling). Each participant will be assigned a specific therapist who will be their care liaison through the program. Each week, the clinician will send the new e-CBT session to the participant through OPTT on a predetermined day of the week. Each of these sessions will include a homework assignment that the participant must send back to their clinician by a predetermined date to gain access to the next session. Upon receiving the homework submission, the clinician will review the participant’s work and provide individualized feedback on their performance. This feedback will be sent back to the participant with their new e-CBT module the following week. Clinician feedback will follow a structured format and take approximately 15 minutes per patient, allowing for increased scalability.

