### Analysis

Qualitative analysis of interview and focus group data (phases 1 and 2) will be performed using an iterative analysis process where investigators will review interview transcripts and search for key phrases, ideas, and themes directly pertaining to the research questions. Similarly, the qualitative comments and feedback obtained from questionnaires in phases 3 and 4 will also be transcribed and analyzed for themes. The information collected in phases 1 and 2 will be used to develop the e-CBT modules, with the information collected through phases 3 and 4 being used to finalize the format of the e-CBT (if necessary).

In phases 3 and 4, the relationship between socioeconomic status, demographic factors, and mental health challenges faced by CWs will be investigated. Questionnaire data will initially be examined for missing, nonsensical, and outlying variables and corrected where possible. Missing data will be treated as missing and not imputed (ie, will be analyzed on a per-protocol basis).

Following this, the symptomatology questionnaires (DASS-42, Q-LES-Q, QIDS-SR16, PHQ-9, GAD-7, and PCL-5) will be analyzed based on score change from baseline to posttreatment, 6-month follow-up, and 12-month follow-up. Questionnaire scores will be calculated for each time point, and then the changes between the times will be assessed using multivariate repeated measures analysis of variance (MANOVA). Comparisons will then be made between the e-CBT and control arms using linear regression models while controlling for demographic variables (eg, age, gender).

Factoring in anticipated dropouts, recruitment numbers have been purposely oversampled. From previous research in similar patient populations, dropouts can be expected to be up to 25% [61]. Given that there are 6 specialized versions of the e-CBT modules with different symptom questionnaires, it is difficult to calculate a single sample size or provide specific power calculations. However, using the PCL-5 as an example as it will be common to all participants, a 10-point change is considered clinically significant [62]. Therefore, a sample size of 30 participants in each arm will be sufficient for detecting significant results with *P*=.05 and a power of 0.8.

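### The claim of 80% power with 30 per arm is unsupported as written: it uses a PCL-5 change threshold as the between-arm difference and assumes, against the Phase 3 text, that everyone completes the PCL-5

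*Protocol article*

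**What the plan says.** The sample size reasoning is in the last paragraph of the Analysis section. It first concedes that "it is difficult to calculate a single sample size or provide specific power calculations", since the six module versions do not share one set of scales. One worked basis is then offered: "using the PCL-5 as an example as it will be common to all participants, a 10-point change is considered clinically significant". The paragraph infers from this, at the .05 level and 80% power, that "a sample size of 30 participants in each arm will be sufficient for detecting significant results". No SD, standardised effect or sidedness is given. The same paragraph expects up to 25% dropout and says that recruitment was oversampled to allow for it.

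Three other sections bear on the claim:

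- **Outcomes:** the primary outcome of Phases 3 and 4 is the change in symptom severity from baseline to week 12, compared between e-CBT and TAU (Phase 3) or in-person CBT (Phase 4).
- **Phase 3 and Phase 4:** each trial randomises 50 per arm. In Phase 4 both arms receive CBT of similar content. The Phase 3 section introduces the scales, PCL-5 included, as "the following clinical questionnaires (primary diagnosis dependent) at baseline".
- **Inclusion/Exclusion Criteria:** participants may have MDD, GAD or PTSD. The expected mix is not stated.

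**The concern.** The conclusion does not follow from its premise, for two reasons that are visible in the text.

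First, the 10 points describe a change that matters clinically, most naturally a change within a person. The trial tests the difference between two arms in their mean change. The two quantities coincide only if the control arm does not change at all. If TAU participants improve, e-CBT participants must improve by 10 points more than that. In Phase 4 the comparator is itself CBT, so the sentence would require a 10-point advantage of one delivery format over the other.

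Second, the calculation treats every participant as a PCL-5 respondent with the same expected benefit. The article disagrees with itself on the first part. The second is an untested assumption, because MDD and GAD participants receive modules built for those diagnoses.

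This sentence is the only justification given for the size of two randomised trials. If it is taken at face value, a null Phase 3 could be read as evidence that e-CBT does not work. A null Phase 4 could be read as comparability with in-person CBT, which the Discussion names as a hoped-for conclusion.

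**Working it through.** **Inputs from the article.** Alpha .05; power 0.80; 30 per arm; 10 PCL-5 points; 50 randomised per arm; dropout up to 25%.

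**Not in the article, so assumed.** Two-sided test; SD of change; share of participants with PTSD; effect on the PCL-5 in MDD and GAD participants.

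**Step 1: what 30 per arm requires.** For a two-sample t-test with n per arm, two-sided .05 and power 0.80, the detectable standardised difference d solves the non-central t equation. With n = 30, d = 0.736. The implied SD is 10 / 0.736 = 13.6. The normal approximation gives nearly the same: SD = 10 / [(1.960 + 0.842) × √(2/30)] = 13.8. So 30 per arm is attainable, but only with an SD that the article does not state. If the test were one-sided, the implied SD would be about 15.4.

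**Step 2: after dropout.** 50 × 0.75 = 37.5, so about 37 per arm. With n = 37, d = 0.660, and 80% power for 10 points holds up to SD = 10 / 0.660 = 15.1. In the other direction, 30 / 0.75 = 40, so 50 per arm more than covers the stated dropout.

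**Step 3: power for a true 10-point between-arm difference in everyone (non-central t).**

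| Assumed SD of change | 30 per arm | 37 per arm |
|---|---|---|
| 12 | 0.89 | 0.94 |
| 13.6 | 0.80 | 0.88 |
| 15 | 0.72 | 0.81 |
| 18 | 0.56 | 0.66 |
| 20 | 0.48 | 0.56 |

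**Step 4: a between-arm difference below 10.** At SD 13.8 (normal approximation), a difference of 7.5 needs 54 per arm and has power 0.65 with 37. A difference of 5 needs 120 per arm and has power 0.34 with 37.

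**Step 5: who completes the PCL-5.** Assume, for illustration, that one third of participants have PTSD.

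- *Only the PTSD third completes it:* 100/3 × 0.75 / 2 = 12.5 per arm. At SD 13.6, power for 10 points is 0.41 with 12 per arm and 0.44 with 13.
- *Everyone completes it, with 10 points in the PTSD third and f points in the rest:* mean difference = 10 × 1/3 + f × 2/3. At SD 13.6 and 37.5 per arm:

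| f | Mean difference | Power |
|---|---|---|
| 0 | 3.3 | 0.18 |
| 3 | 5.3 | 0.39 |
| 5 | 6.7 | 0.55 |

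**The case against.** A reader might infer that the trial is underpowered and that the stated 80% is not delivered. The article does not support that. It fixes neither the SD, nor the PTSD share, nor the effect outside PTSD, so no shortfall can be demonstrated. If the true between-arm difference is 10 points in everyone, 80% power holds at any SD up to about 13.6, and up to about 15.1 with 37 completers per arm. At SD 12 the power is 0.89 even with 30. Randomising 50 per arm is a real margin over the 40 that 25% dropout requires. The low powers in Step 5 are sensitivity cases. One of them assumes that only PTSD participants complete the PCL-5, which the Analysis section denies; the lowest assumes no benefit at all on the PCL-5 for MDD and GAD participants, although all modules share standard CBT elements.

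It is also fair to say that the article calls the PCL-5 an example, that it condenses a fuller protocol, and that a missing SD could be stated there. For that reason the missing SD alone would not be a finding. Nor would the fact that six scales are named as primary while power is given for one test, since a multiplicity rule may sit in an analysis plan that is not shown.

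What these arguments leave untouched is what the article itself asserts: a change threshold, followed by a therefore, used to size a between-arm comparison in two trials with different comparators, on a premise that another section contradicts.

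**Conclusion.** The concern stands in a limited form, as something that should be fixed. The statement of 80% power with 30 per arm is unsupported as written. It holds at two-sided .05 only if two conditions are met together: the SD of change is at most about 13.6 (about 15.1 with 37 evaluable per arm), and a full 10-point difference between arms applies across all three diagnoses. The article justifies neither. The second is hardest to accept in Phase 4, where the comparator is active CBT.

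The premise that the PCL-5 is common to all participants contradicts the Phase 3 section. Under the assumed one-third PTSD share and SD 13.6, power would be about 0.41 to 0.44 if only that third completed the scale. It would be about 0.18 to 0.55 if everyone did and the others gained 0 to 5 points. These ranges show how much the answer depends on unstated inputs; they do not estimate the trial's actual power. The planned number of participants is not shown to be wrong.

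**What to change.** Keep n=100 in each trial and rewrite the sample size paragraph.

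1. Replace the sentence with what the design can detect: with about 37 evaluable per arm, a between-arm standardised difference of about 0.66 at 80% power, two-sided .05, for a single test. Alternatively, state an assumed between-arm difference and an SD of change with its source, and recompute.
2. Reconcile the Phase 3 and Analysis sections on who completes the PCL-5. If it is completed by PTSD participants only, the 37 per arm in item 1 no longer applies and the detectable difference must be recalculated from the evaluable number that results.
3. Give Phase 4 its own statement, with a difference that makes sense against in-person CBT, and say plainly that a non-significant result there does not show comparability.

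The cost is one rewritten paragraph and no added participants. The downside is that the stated power will look less favourable than it does now.

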### Ethics and Data Privacy

Only the care providers directly involved in participant interaction will be able to access their information. Participant identity will be kept anonymous through randomized participant ID numbers on OPTT. OPTT is compliant with the Health Insurance Portability and Accountability Act, the Personal Information Protection and Electronic Documents Act, and the Service Organization Control - 2. Additionally, all servers and databases are hosted in Amazon Web Service Canada cloud infrastructure, which is managed by Medstack to assure all provincial and federal privacy and security regulations are met. OPTT will not collect any identifiable personal information or internet protocol addresses for privacy purposes. OPTT will only collect anonymized metadata to improve its service quality and provide advanced analytics to the clinician team. All encrypted backups will be kept on secure Queen’s University servers.

## Results

The study received notice of funding acceptance in March 2020. Ethics approval from the Queen’s University HSREB (File Number: 6029966) was obtained in December 2020. Participant recruitment began in March 2021 using targeted advertisement and physician referrals (see the Recruitment section). To date, there have been 15 participants recruited for Phase 1, and it is expected to conclude in June 2021 with phase 2 beginning in September 2021. Complete data collection and analysis from all phases are expected to conclude by July 2023. Focus group analysis described earlier will be conducted after phases 1 and 2, and regression analysis (continuous and categorical outcomes) will be conducted after phases 3 and 4. All procedures and outcomes have been and will be reported using the GUIDED (Multimedia Appendix 1) and TIDieR Report Guidelines (Multimedia Appendix 2).

## Discussion

CWs are at a significantly elevated risk of developing a mental health disorder. Due to stigma, geographic isolation, cost, and irregular work hours, CWs are less likely to seek treatment for their mental health struggles. To address this, innovative treatments are needed. CBT is an effective treatment; however, it is not readily available to CWs due to long wait times. The delivery of CBT through the internet is a promising solution. The outcomes of this study can both improve our understanding of CW mental health challenges and provide an innovative approach to address them. Focus group discussions will explore specific challenges each group of CWs face so therapy modules can be designed and targeted accordingly. The comprehensive mental health evaluations will also provide an invaluable survey of the mental health status of CWs.

If proven effective, e-CBT could be an accessible option for CWs to receive care whenever, wherever, and in any language they need without worrying about the stigma of receiving care. If shown to be comparable to in-person CBT, this method of care delivery could massively expand the therapy capacity in the public sector without sacrificing the quality of care.

This project has the potential to influence clinical care and health care policy by addressing barriers currently preventing CWs from receiving the care they need. This approach would offer monetary savings to the health care system and provide a more equitable and accessible method of delivery. Asynchronous e-CBT takes less time for the clinician to deliver, while still providing comprehensive benefits of therapy with added accessibility and efficiency. This increased efficiency can allow clinicians to be more productive within their clinical time and workload.

## Appendix

Multimedia Appendix 1 GUIDED Report Checklist.

Multimedia Appendix 2 TIDieR Report Checklist.

Multimedia Appendix 3 Funding acceptance letter and reviewer comments from the Canadian Institutes of Health Research.

## Abbreviations

CBT: cognitive behavioral therapy
CW: correctional worker
DASS-42: Depression and Anxiety Stress Scale - 42 Item
DSM-5: Diagnostic and Statistical Manual of Mental Disorders, 5th Edition
e-CBT: electronically delivered cognitive behavioral therapy
GAD-7: Generalized Anxiety Disorder - 7 Item
HSREB: Health Science and Affiliated Teaching Hospital Research Ethics Board
MANOVA: multivariate repeated measures analysis of variance
MDD: major depressive disorder
MINI: Mini-International Neuropsychiatric Interview
OPTT: Online Psychotherapy Tool
PCL-5: PTSD Checklist for the DSM-5
PHQ-9: Patient Health Questionnaire - 9 Item
PSP: public safety personnel
PTSD: posttraumatic stress disorder
QIDS-SR16: Quick Inventory of Depressive Symptoms Self Report - 16 Item
Q-LES-Q: Quality of Life Satisfaction and Enjoyment Questionnaire
RCT: randomized controlled trial
TAU: treatment as usual
